**Summary**

| Title | Improving Adherence to Immunosuppressive Therapy using a Mobile Internet Application in Solid Organ Transplant Patients  (PRIMA study) |
| --- | --- |
| Principal Investigator | [name]  Dept. of Surgery, Seoul National University College of Medicine |

| Purpose | To develop a mobile internet application that assists with medication in immunosuppressive therapy to improve immunosuppressant adherence in organ transplant patients |
| --- | --- |
| Study Period | Date of IRB approval – 2 years post-IRB approval |
| Subjects | Renal transplant recipients |
| Methods | 1. Development of a mobile internet application that assists with medication. 2. A randomized clinical trial is carried out, where 138 post-transplantation patients currently taking immunosuppressants are divided into a control group (69 patients) and a test group (69 patients) who are requested to use the newly developed application.  3. Adherence to immunosuppressants is assessed using an electronic pillbox (MEMS®). |
| Expected Outcome | Through this study, a mobile internet application will be developed to improve patients’ adherence to medication. The use of the application is likely to minimize nonadherence, the most important cause of preventable transplanted organ loss after transplantation, while allowing long-term survival of the transplanted organ. |

Astellas Pharma Inc. in Korea

Location: [name]
Contact no.: [name]

1. **Expected duration of the clinical trial**

Date of IRB approval – 3 years post-IRB approval

1. **Subjects**

Renal transplant recipients

1. **Background and purpose**

**1) Background**

Adherence to post-transplantation medication has a profound influence on the prognosis of the transplanted organ. In particular, irregular doses of immunosuppressants result in low suppression of immunity which in turn causes acute or chronic rejection and antibody-mediated rejection, thereby inducing chronic organ damage eventually leading to the loss of the transplanted organ. In a meta-analysis of patients with a chronic disorder, nonadherence resulted in a 24.8 % morbidity. In transplant patients, the average nonadherence rate was 22.6 cases per 100 person/year, but it could reach as high as 53% in renal transplant patients and adolescent patients. According to the joint meeting report of the American Society of Transplantation, the American Society of Transplant Surgeons, Health Services and Resource Administration, the American Society of Nephrology, the International Pediatric Transplant Association, UNOS and NATCO, adherence is defined as ‘the extent to which the patient’s behavior matches the agreed upon prescriber’s recommendations’ while in another study, it is defined as ‘the extent to which the patient follows the prescribed dose and interval of medication’. Although improving the adherence to immunosuppressants in transplant patients is the most effective way to lower the risk of preventable graft loss, only a few effective methods have been developed to improve medication adherence. At present, nine different types of mobile internet applications are available, all of which have been developed for patients in an English-speaking country and are therefore not suitable for use by Korean patients. The available applications are as follows:

HealthPrize (iPhone and Android; free)
Pillboxie (iPhone; free)
MediRemind (iPhone, Blackberry and Android; $0.99)
Dosecast (iPhone; free)
MotionPHR Health Record (iPhone and Android; $9.99)

Medsy (iPhone; $1.99)
Rxmind Me (iPhone; $1.99)
MedCoach (iPhone and Android; free)

**2) Purpose**
To develop a mobile internet application aimed at improving medication adherence of Korean patients.

1. **Selection criteria & sample size and rationale**
2. **Inclusion criteria**
   • Patients who received organ transplantation at Seoul National University Hospital and are currently in outpatient follow-up monitoring
   • Patients who are android smartphone users
   • Patients who received transplantation ≥1 year prior to the study
   • Patients who are currently taking a calcineurin inhibitor (Tacrolimus or Cyclosporine) as their principal immunosuppressant
   • Patients aged between 15 and 70
3. **Exclusion criteria**

• Patients who are unable to use MEMS®
• Patients who received multiple organ transplants
• Patients whose immunosuppressant was changed within four weeks of enrollment
• Patients whose medication regimen is under caregiver management
• Patients who are unable to use the application function of the smartphone
• Patients who are pregnant or are planning pregnancy

1. **Sample size and rationale**

The present study targets 138 patients who underwent organ transplantation at Seoul National University Hospital and are currently taking an immunosuppressant under outpatient follow-up monitoring. The control and test groups have 69 subjects each.

The lack of studies on medication adherence in transplant patients in Korea makes it difficult to verify the level of adherence in Korean patients. Most previous studies on adherence, in overseas transplant patients, targeted 30–60 subjects, who showed 40%–70% adherence before behavioral intervention and 80%–95% adherence after behavioral intervention (Bleser LD, transplant international 2009). However, in consideration of the differences between overseas national insurance systems and the system in Korea where insurance covers all post-transplantation immunosuppressants, the nonadherence rate was assumed to be 30 % in the control group and 10 % in the test group. Based on MRCC consultation, the significance level was set at α = 0.05 and type II error (β) was set at 0.20 so that the power of the test was 80 %, resulting in the need for an estimated 125 subjects (62 per group). Estimating a 10 % dropout rate, the sample size was determined to be 138 (69 per group).

1. **Methods**
2. **Detailed description**

1. A mobile internet application for improving medication adherence (proposed name, Adhere4U) will be developed, whose functions include:

① Notifications of the times to take the medication (alarm, etc.)
② Encouraging the patient to check the times to take medication
③ Checking the test results (period can be set)
④ Allowing the data to be shared with the physician given the patient’s consent
⑤ Privacy protection: Deletion of all data upon the loss of the phone, etc.
⑥ A little game function

- The application does not have any functions that require the patient to provide personal information such as a request for membership, etc.
2. The subjects will be 138 patients (69 in both the control and test groups) who received organ transplantation at Seoul National University Hospital, are in outpatient follow-up monitoring, and who have been selected based on the selection criteria.
3. All patients will be requested to perform a self-reported assessment of adherence to immunosuppressant and comedication on day 0, 28, 90, and 180 using the Basel Assessment of Adherence with Immunosuppressive medication Scale (BAASIS) and the Visual Analog Scale (VAS). The adherence to immunosuppressant will be assessed by drug dose (tacrolimus or cyclosporine trough level) on day 0, 28, 90, and 180 using the medication event monitoring system (MEMS®). Also, to identify the psychosocial characteristics among the baseline characteristics, Hospital Anxiety and Depression Inventory (14 item, Oh et al.) and Personality Traits (BFI-K-10, Kim et al.) will be assessed.

4. The subjects in the control group will be requested to only use MEMS®, while those in the test group will be asked to use MEMS® and the newly developed mobile internet application simultaneously.

5. The allocation of subjects to the control and the test groups will use the web-based randomization of MRCC.

6. A longitudinal assessment of the improvement in adherence will be carried out over the 6-month period following randomization.

.

1. **Method of selecting the control and randomization**

The control of this clinical study consists of patients who are requested to only use MEMS®.

• Group 1: Control group; patients requested to only use MEMS®
• Group 2: Test group; patients requested to use MEMS® and the mobile internet application adhere4U simultaneously

For random allocation of subjects, the web-based program (<http://mrcc.snu.ac.kr>) of MRCC will be used for 1:1 randomization of the control and the test groups.

1. **Methods of monitoring and the monitored items and clinical test items**

| **Visit Schedule & Assessed Items** | | | | |
| --- | --- | --- | --- | --- |
| **Item** | **Screening**  **(Day 0)** | **Day 28** | **Day 90** | **Day 180** |
| **Informed Consent Form** | **√** |  |  |  |
| **Patient Data** | **√** |  |  |  |
| **Medical Checkup** | **√** | **√** | **√** | **√** |
| **Physical Examination** | **√** | **√** | **√** | **√** |
| **App Download (Test Group)** | **√** |  |  |  |
| **Training for App Use (Test Group)** | **√** | **√** | **√** | **√** |
| **MEMS^®^ Distribution** | **√** |  |  |  |
| **Training for MEMS^®^** | **√** | **√** | **√** | **√** |
| **Blood Test** | **√** |  |  | **√** |
| **Blood Chemistry Test** | **√** |  |  | **√** |
| **Estimated GFR (by MDRD)** | **√** |  |  | **√** |
| **Acute Rejection** | **√** | **√** | **√** | **√** |
| **Therapeutic Drug Monitoring** | **√** | **√** | **√** | **√** |
| **HAD-K, BFI-K-10** | **√** |  |  |  |
| **BAASIS with VAS** | **√** | **√** | **√** | **√** |
| **Electronic Monitoring** | **√** | **√** | **√** | **√** |

- The clinical test items include the following:

• Blood test: WBC with differential count, Hemoglobin, Hematocrit, RBC, Platelets
• Blood chemistry test: Renal function test (sodium, potassium, calcium, phosphorus, BUN, Creatinine), glucose, uric acid, AST, ALT, ALP, albumin, total bilirubin

• Serious adverse events (SAE):
 ▪ A fatal or life threatening event
 ▪ An event resulting in continuous or serious disability or incompetency
 ▪ An event requiring hospitalization or prolonged length of stay
 ▪ A medical emergency case (where medical or surgical treatment is required)
• Acute rejection refers solely to cases diagnosed by histological examination. Renal histological examination to confirm acute rejection may be carried out on cases showing two or more consecutive rises over 30 % of the baseline serum creatinine or where a medical professional admits the necessity of the examination.

• HAD scale

**Hospital Anxiety and Depression Scale**

Age: Gender: male / female

*Your emotional state may have substantial influence on your health or the disorder.

*Read each item and circle the reply that comes closest to how you have been feeling.

[figure not shown]

• BFI-K-10

**Big Five Inventory – Korean Version (BFI-K-10)**

Here are some questions that may relate to your personality. For each item

I am about to describe to you, reply with a score that best represents your personality.

| 1  Not at all | 2  Not so much | 3  Normally | 4  Frequently | 5  Definitely |
| --- | --- | --- | --- | --- |

“I consider myself to be__________.”

1. *__________ conventional/conservative

2. ___________ trustworthy

3. *__________ lazy

4. *__________ easygoing (capable of managing stress easily)

5. *__________ unartistic (having little interest in art)

6. ___________ outgoing and sociable

7. *__________ critical of others

8. ___________ thorough in the given tasks

9. ___________ irritable

10. __________ imaginative

• Basel Assessment of Adherence with Immunosuppressive medication scale (BAASIS) (Schafer-Keller P et al Am J Transplant 2008, Deschamps AE et al AIDS Patient Care STDS 2004, Kerr T et al AIDS Care 2005)

: Assessment of adherence over the past four weeks; 1-5 is defined as nonadherence

**<Basel Assessment of Adherence with Immunosuppressive medication scale (BAASIS)>**

| Question | 0  Never | 1 | 2 | 3 | 4 | 5  Always |
| --- | --- | --- | --- | --- | --- | --- |
| On one or several days in the past four weeks, I have forgotten to take the immunosuppressant. |  |  |  |  |  |  |
| On one or several days in the past four weeks, I have taken the immunosuppressant two hours before or after the prescribed time of medication. |  |  |  |  |  |  |
| On two or more consecutive days in the past four weeks, I have forgotten to take the immunosuppressant. |  |  |  |  |  |  |
| On one or several days in the past four weeks, I have taken the immunosuppressant in the dose lower than the prescribed dose. |  |  |  |  |  |  |

• VAS (Visual analogue scale)

전혀 복용 안함: Never took any medication

완벽히 복용함: Took all medications perfectly

[figure not shown]

• MEMS ® parameters: Automatically extracted using MEMS®

1) Taking adherence: percentage of cap removals compared with the number prescribed for the monitoring period
2) Dosing adherence: percentage of days on which the patient took the prescribed number of doses
3) Timing adherence: percentage of correct dosing intervals (**±** 1 hour of prescribed intake timing)
4) Number of drug holidays: no cap removals over a period greater than 24 h

1. **Adherence assessment**

The assessment of medication adherence will be based on MEMS® and BAASIS. On the day of screening visit, the patient will be trained in the use of MEMS®, and for the test group, the mobile internet application will be installed on the patient’s phone and the patient trained in its use. On Day 28 (Study visit 1), current use of MEMS® and the app will be checked and retraining provided. On Day 90 (Study visit 2), current use of MEMS® and the app will be checked once again. On this day, the adherence rate recorded by MEMS® will not be disclosed to the patient, while (s)he will be informed of the cases of inappropriate use and retraining provided.

1. **Methods and variables of efficacy evaluation and reporting**

To verify whether the use of the mobile internet application has led to improved adherence to immunosuppressants, the following will be assessed:

- Primary endpoint: Evaluation of the differences in 6 months nondherence rate (assessed by MEMS®) between groups after the onset of study.

• Nonadherence: a taking adherence of <98% or >102% and/or at least one drug holiday

- Secondary endpoints: Determination of the factors that influence the adherence rate based on demographic, socioeconomic, medical, and surgical factors as well as those identified by HAD-K and BFI-K-10, for which the Collateral monitoring (BAASIS with 120 mm VAS, tacrolimus or cyclosporine trough level, and the adherence rate on the app) and MEMS® are used to evaluate the correlations among the assessed adherence rates and the variations in the incidence of acute rejection and eGFRMDRD between the groups.

1. **Statistical analysis: principles and methods**

MRCC was consulted for the methods of randomization and statistical analysis.

1) Subject group
The data analysis of the differences in the rate of incidence of acute rejection and the variations in eGFRMDRD, among primary and secondary efficacy evaluation items, requires randomization and non-violation of the protocol, and targets the patients per protocol (PP) who have completed all visits during the six-month period. Also, the secondary efficacy evaluation targets all randomized patients who used MEMS®.

2) Statistical analysis
The differences in adherence rate between groups will be compared using a chi-square test. Subjects will be grouped by adherence rate (>95-100%, 80-95%, 50-80%, and 0-50%), to evaluate the factors influencing adherence including demographic, socioeconomic, medical, and surgical factors, based on a multivariable ordinal logistic regression model. SPSS version 17.0 will be used.

1. **Data and Safety Monitoring Plan**
2. **Monitoring**
   The participants of the study should review the clinical study protocol and the case report at the initiation meeting prior to the onset of study. During the study period, the sub-investigator will check the completeness of patient records, the accuracy of the case reports, and the clinical study protocol and enrollment status, every three months until the termination of study in order to make sure that the study is in compliance with the protocol. The investigator will maintain the documents containing the demographic, medical, and lab data, and a record of other test results and evaluation results, per each subject. All data included in the case report should be traceable based on the documents in each subject’s file. The investigator will store the original copy of the informed consent form signed by the subject, while a single copy of the signed form will be given to the subject. The monitoring criteria requires the standard verification of all data that may be used as a variable in efficacy evaluation, as well as keeping the consent forms, the compliance to inclusion/exclusion criteria, and the record of SAEs. No data in the evidential documents regarding subject identity may be disclosed.
3. **Data storage**
   The investigator should maintain an appropriate and accurate record of the contents of the study to allow future access to any of the data related to the study. All data and documents related to the study should be stored in a place with limited access, open only to IRB personnel or relevant staff. The documents related to the study should be stored in files for a minimum of ten years after the completion or termination of study. The documents may be discarded once the period of ten years has expired.
4. **Privacy protection for subjects**

To prevent any leakage of personal information due to the loss of the smartphone, etc., the original data may be deleted via the internet.

1. **Study protocol schedule**

1) Date of IRB approval – 2 years post-IRB approval
2) For 3 months post-IRB approval: Development of the mobile internet application
3) Month 3 to 4 post-IRB approval: Test trial of the application
4) Month 4 to 24 post-IRB approval: Patient enrollment
5) Month 4 to 30 post-IRB approval: End of patient follow-up
6) Month 30 to 36 post-IRB approval: Data interpretation and research presentation

1. **Other ethical and scientific considerations**

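### The primary chi-square test is valid, but it makes no use of the Day 0 self-reported adherence already collected; stratifying on it is a nearly free gain in power of uncertain size

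*Protocol*

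**What the plan says.** The primary endpoint is "Evaluation of the differences in 6 months nondherence rate (assessed by MEMS®) between groups after the onset of study", where nonadherence means "a taking adherence of <98% or >102% and/or at least one drug holiday". Each patient therefore contributes one yes/no outcome. The only between-group method named is in Statistical analysis: principles and methods: "The differences in adherence rate between groups will be compared using a chi-square test".

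On baseline data, item 3 of the detailed description under Methods states: "All patients will be requested to perform a self-reported assessment of adherence to immunosuppressant and comedication on day 0, 28, 90, and 180". The instruments are BAASIS and VAS, and the visit schedule ticks them at Day 0. BAASIS is described as "Assessment of adherence over the past four weeks; 1-5 is defined as nonadherence", so the Day 0 score looks back over the weeks before the study. The endpoint instrument has no such baseline: MEMS is handed out at Day 0 and "On the day of screening visit, the patient will be trained in the use of MEMS", with no run-in.

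Allocation is web-based and 1:1, with no stratification factor described. The one covariate model, "based on a multivariable ordinal logistic regression model", looks for factors that influence adherence. It is separate from the group comparison, and baseline adherence is not among its listed factors. BAASIS does have another use, within "Collateral monitoring (BAASIS with 120 mm VAS, tacrolimus or cyclosporine trough level, and the adherence rate on the app"), which is to be correlated with the MEMS results.

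**The concern.** Past medication-taking is a natural candidate to predict later medication-taking. Three of the four BAASIS items concern missed or reduced intake, which overlaps with what the MEMS endpoint counts. If the Day 0 score does predict the outcome, a test that conditions on it has more power than one that does not, at the same sample size and type I error. It also removes the effect of chance imbalance in prior adherence from the estimate, which matters more where the design is not described as balancing that factor.

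The trial is planned at 80% power with about 62 evaluable patients per arm, so a few points are worth having. The adjustment has to be prespecified: one chosen after the data are seen is open to challenge.

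**Working it through.** **1. The plan's own figure.** Inputs from Sample size and rationale: 30% versus 10% nonadherent, α = 0.05 (sidedness not stated; two-sided reproduces the figure), β = 0.20, 10% dropout.

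n per arm = [1.960 × √(2 × 0.20 × 0.80) + 0.842 × √(0.30 × 0.70 + 0.10 × 0.90)]² / 0.20² = 61.6, so 62. Then 62 / 0.90 = 68.9, so 69 per arm and 138 in total.

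This matches the protocol, so the planned test and the sample size agree. By the same formula, power is 80.3% at 62 per arm and 84.3% at 69.

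**2. What must be assumed.** The protocol gives neither the share of patients nonadherent on Day 0 BAASIS (q) nor the association of that score with 6-month MEMS nonadherence (odds ratio, OR). I took q = 30% or 50% and OR = 1, 2, 4, 8 and 16, the same OR in both arms. For each pair, the stratum rates were solved so that the arm totals stay at 30% and 10%. For example, at q = 30% and OR = 4 the control rates are 20.9% and 51.3%, and 0.7 × 20.9 + 0.3 × 51.3 = 30.0. The control-arm correlation is phi = (p₁ − p₀) × √(q(1 − q)) / √(0.30 × 0.70).

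**3. Comparison of the two tests.** Simulation, 40,000 trials per setting: the unadjusted chi-square test against a Mantel-Haenszel test in two Day 0 BAASIS strata. At 62 per arm:

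| OR | q | phi | Unadjusted power | Stratified power | Gain (points) |
|---|---|---|---|---|---|
| 1 | 30% | 0.00 | 81.2% | 81.3% | 0.1 |
| 1 | 50% | 0.00 | 81.3% | 81.5% | 0.2 |
| 2 | 30% | 0.15 | 81.0% | 81.8% | 0.8 |
| 2 | 50% | 0.16 | 80.9% | 81.8% | 0.9 |
| 4 | 30% | 0.30 | 81.2% | 84.1% | 2.9 |
| 4 | 50% | 0.30 | 81.3% | 83.8% | 2.5 |
| 8 | 30% | 0.45 | 81.3% | 87.0% | 5.7 |
| 8 | 50% | 0.42 | 81.2% | 85.9% | 4.7 |
| 16 | 30% | 0.57 | 81.3% | 90.7% | 9.4 |
| 16 | 50% | 0.51 | 81.2% | 87.7% | 6.5 |

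At 69 per arm (no dropout) the unadjusted test has about 86%. The stratified test has 85% to 86% at OR 1 to 2, 87% to 88% at 4, 89% to 91% at 8 and 91% to 94% at 16. The largest loss in any setting is about 0.4 points, at OR 1.

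**4. Type I error.** With 20% in both arms, the unadjusted test rejects in 4.6% to 5.2% of trials and the stratified test in 4.8% to 5.2%, across all settings at 62 and 69 per arm.

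**5. Chance imbalance.** The standard deviation of the between-arm difference in Day 0 nonadherence is √(2q(1 − q)/62): 0.082 at q = 30% and 0.090 at q = 50%. By the normal approximation, a difference of 10 points or more arises in 22% and 27% of trials (20% and 24% if the counts are treated as discrete). Such an imbalance shifts the observed risk difference by about 10 × the mean, over the two arms, of the stratum difference. At q = 30% this is 10 × (0.304 + 0.140)/2 = 2.2 points for OR 4 and 10 × (0.448 + 0.204)/2 = 3.3 points for OR 8. At q = 50% it is 1.9 and 2.7. The planned difference is 20 points.

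**The case against.** The best reply is that nothing here is wrong. Under 1:1 randomisation the chi-square test keeps its type I error, random imbalance is already allowed for in that error rate, and the sample size was computed for exactly this test. The stated power is delivered, and only an optional bonus is left aside. All of that stands.

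The reply also limits how much may be claimed for the covariate. A reader might infer that Day 0 BAASIS is the strongest prognostic factor collected. The protocol does not rank it, gives no association, and says that adherence in Korean patients is hard to verify. The two measures also differ. BAASIS is a four-week self-report that counts any score of 1 to 5 and includes a timing item. The endpoint covers six months of cap openings, has no timing component and counts over-taking, which no BAASIS item asks about. A weak association is therefore possible, and the gain would then be close to nil.

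A reader might also infer that BAASIS is the only baseline adherence measure, that its data go unused, or that randomisation is simple. None of these is supported. VAS and trough level are also taken on Day 0, BAASIS enters the secondary correlations, and the randomisation method beyond web-based 1:1 is not described.

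Finally, an adjusted sensitivity analysis may be in a statistical analysis plan that is not shown. That would not change the primary test, which the protocol itself fixes without adjustment.

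**Conclusion.** The point holds as a recommended improvement, not as an error. The primary test ignores a baseline adherence measure that is scheduled for every patient, in a trial whose endpoint instrument has no baseline and whose randomisation is not described as stratified. At 62 per arm, stratifying moves power from about 81% to somewhere between 81% and 91%. The gain is 0 to 3 points for odds ratios up to 4, and about 5 to 9 points only if the association is strong (8 to 16). Type I error stays near 5%.

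The range rests on assumed odds ratios, an assumed 30% to 50% nonadherent at Day 0, and the protocol's 30% versus 10%. The documents cannot narrow it. What makes the change worth making is the asymmetry: almost nothing is lost if the association is absent, and there is a useful gain if it is moderate or strong.

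A reader might extend the criticism to the eGFR comparison. The documents do not support that: the protocol names no eGFR method, and the choice may properly sit in the statistical analysis plan.

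**What to change.** - In Statistical analysis: principles and methods, name as the primary test a Cochran-Mantel-Haenszel test of 6-month MEMS nonadherence between groups, stratified by Day 0 BAASIS nonadherence (any item scored 1 to 5 versus none).
- Report the stratified risk difference with its 95% CI. Keep the plain chi-square test as a supportive analysis.
- State in the visit schedule that the Day 0 BAASIS is completed before allocation. The schedule puts it at the same visit as the app download and gives no order.

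The sample size can stay at 138, since it already gives the planned power without adjustment. No new data are needed. The cost is a change of protocol wording, because the chi-square test is fixed there, and it should be made before any outcome data are examined by group.
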